### Sample Size Determination

#### Sample Size for the ANC Visit

The method suggested by Hooper et al [34] for cluster randomized trials with repeated cross-sections was used for the calculations. This method requires calculating 2 design effects, which are then used to inflate the sample size for individual randomization to account for the within-period intracluster correlation coefficient (ICC) and the between-period ICC. A sequence of steps has been followed to get the final sample size for the current 3-arm cluster randomized trials with repeated cross-sections. For ANC, we first calculated the individual randomization trial using the following assumptions: P1—the proportion of women attending ANC for more than 4 visits among the control group 23.27% [35], power=80%, 2-sided α=0.025, effect size=15%, and Zα/2 adjusted for multiple comparisons using a Bonferroni correction of 2.24. Individual randomization sample size (n) is calculated as follows:

Next, the design effect (*d*_c_) due to cluster randomization was calculated as *d_c_* = 1 + (*m* – 1)*ρ*. Here, the following parameters were considered: the within-period ICC(*p*) was assumed to be 0.003 [36], and the cluster size (m) was assumed to be 28. The calculation yielded a design effect due to cluster randomization *dc* = 1 + (*m* – 1)*ρ* = 1.08. Additionally, the design effect due to repeated assessment was calculated as *d*_r_=(1–*r*^2^), where *r* is the correlation between samples from the same cluster at different times and determined as 
[figure not shown]
. Based on this, *d*_r_ was calculated using assumptions: within-period ICC=0.003, autocorrelation coefficient (π) of 0.8 (to allow for a 20% decay of the correlation from within to between different periods) [37], and *m*=28 and 
[figure not shown]
=0.062. Thus, the design effect due to repeated assessment was *d*_r_=(1–*r*^2^)=0.996.

To arrive at the final sample size per arm, the sample size for individual randomization is multiplied by both design effects, resulting in (n×*d*_c_×*d*_r_)=188. Considering a 4% loss to follow-up, the final sample size for each arm is 196 and this gives a total sample size of 588 when ANC was used as the primary outcome of the intervention.

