#### Sample Size for Newborn Practice

For newborn care practice, the same procedure described earlier was used. First, the individual randomization sample size was calculated to be 118 based on the following assumptions: P1—the proportion of exclusive breast feeding among the control group of 74.8% [38], power=80%, 2-sided α of 0.025, effect size=15%, and *Z*α/2 adjusted for multiple comparisons using a Bonferroni correction=2.24. Then, the design effect (*d*_c_) due to cluster randomization was calculated as *d_c_* = 1 + (*m* – 1)*ρ* = 1.35 by considering the following parameters: within-period *p* of 0.013 [39] and cluster size assumed to be 28. The design effect due to repeated assessment was calculated as *d*_r_=(1–*r*^2^)=0.953, where the correlation between samples from the same cluster at different times *r*=0.251 by using assumptions: within-period ICC=0.013 [39], autocorrelation coefficient (π) of 0.8 (to allow for a 20% decay of the correlation from within to between different periods) [37], and *m*=28. By inflating the sample size under individual randomization with the 2 design effects as (n×*d*_c_×*d*_r_)=152. Considering a 4% loss to follow-up, the total sample size was 475.

Therefore, the sample calculated for ANC was larger (588) and was the final sample size of the trial to arrive at 21 clusters (7 per arm) and an average of 28 eligible pregnant mothers.

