### Operational Definitions

Operational definitions are as follows:

Maternal health service usage:when mothers receive at least 8 ANC follow-up visits, give birth in a health facility, and visit a health facility for PNC follow-up contact from health professionals within 7 days of delivery.Newborn care practice:this refers to the care provided to the baby from birth to 28 days of age by the mothers, including early initiation of breastfeeding, exclusive breastfeeding, feeding colostrum, thermal care, hygienic cord care, and seeking care for an ill newborn. If a mother feeds colostrum, initiates breastfeeding within 1 hour after birth, feeds a newborn only breast milk, practices thermal and hygienic cord care, and seeks care for her ill newborn, she is considered to be practicing newborn care, and if she misses one of them, she is considered to be not practicing newborn care.Knowledge about maternal health services:participants were asked to mention the recommended newborn care practice using 16 questions. All the responses were counted, and the higher score indicates a higher knowledge of newborn care practice.Knowledge of maternal danger signs:this was measured by 7 items related to maternal danger signs during pregnancy, labor & delivery, and the postnatal period such that yes=1 for correct statements and no=0 for incorrect statements. The scores of correct answers were summed, and a higher score was interpreted as a higher level of knowledge of maternal danger signs.Knowledge of newborn danger signs:this was measured by 12 items related to neonatal danger signs, such that yes=1 for correct statements and no=0 for incorrect statements. The scores of correct answers were summed, and a higher score was interpreted as a higher level of knowledge of newborn danger signs.Knowledge of newborn care practice:participants were asked to mention the recommended newborn care practice using 7 questions. All the responses were counted, and the higher score indicates a higher knowledge of newborn care practice.Attitude toward maternal health services:this refers to mothers’ feelings toward maternal care practice. Attitude toward maternal care practice was measured by 10 items on a 5-point Likert scale ranging from 1=strongly disagree to 5=strongly agree. The cumulative scores were used in the analysis once negatively phrased items were reverse-coded. A higher composite score indicated a more favorable attitude toward maternal care practice.Attitude toward newborn care practice:this refers to mothers’ feelings toward newborn care practices. It was measured by 16 items, which are designed in a 5-point Likert scale format ranging from 1=strongly disagree to 5=strongly agree. The sum score was used in the analysis after reverse coding the negatively worded items. The higher composite score was interpreted as a favorable attitude toward newborn care practice.Self-efficacy to practice maternal health service usage:self-efficacy in practicing maternal care is an individual belief in mothers’ ability to perform maternal care practices. It was measured by 10 items designed on a 5-point Likert scale ranging from 1=strongly disagree to 5=strongly agree. Once negatively worded items were reverse-coded, the sum score was used in the analysis. A score with a high value indicated greater self-efficacy in practicing maternal care.Self-efficacy to practice maternal and newborn care:this refers to an individual belief in one’s ability to perform maternal and newborn care practice. It was measured by 9 items, which are designed in a 5-point Likert scale format ranging from 1=strongly disagree to 5=strongly agree. The sum score was used in the analysis after reverse coding the negatively worded items. A score with a high value indicates higher self-efficacy toward practicing newborn care.

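### The 80% power and the 588 women were derived for more than 4 ANC visits and for exclusive breastfeeding alone, so power is not established for the composite primary outcomes

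*Protocol article*

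**What the plan says.** The protocol article names two primary outcomes, maternal health service usage and newborn care practice (Abstract; Outcomes).

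Operational Definitions makes both of them composites. Maternal health service usage is met "when mothers receive at least 8 ANC follow-up visits, give birth in a health facility, and visit a health facility for PNC follow-up contact", the last within 7 days of delivery. Newborn care practice needs every listed behaviour: colostrum, breastfeeding in the first hour, breast milk only, thermal care, cord care, and care-seeking when the newborn is ill; "and if she misses one of them, she is considered to be not practicing newborn care".

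Sample Size Determination uses other outcomes. For the maternal side it takes "the proportion of women attending ANC for more than 4 visits among the control group 23.27"%, with "power=80%, 2-sided α=0.025, effect size=15"% and a critical value "adjusted for multiple comparisons using a Bonferroni correction of 2.24". This gives 188 per arm, 196 after 4% loss, and 588 in total. For the newborn side it takes "the proportion of exclusive breast feeding among the control group of 74.8"% with the same power, alpha and effect, which gives 152 per arm and 475 in total. The larger figure is adopted as the trial's sample size.

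**The concern.** A sample size supports a power statement only for the outcome whose control proportion, effect and ICC went into it. Here both calculations use something less demanding than the outcome defined. On the maternal side the ANC threshold is lower (more than 4 against at least 8) and two further conditions are left out. On the newborn side one behaviour stands in for six. A composite cannot be more common than its rarest component, so if the cited rates apply, the control proportions are at most 23.27% and 74.8%. How far below they lie is not stated anywhere.

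At stake is how the result is read. The conclusions direct the evidence to policy makers. A null finding on either composite could be taken as coming from a trial with 80% power for that outcome, when no such power has been shown.

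**Working it through.** **Inputs.** All come from Sample Size Determination: two-sided alpha 0.025 (critical value 2.24), power 80% (0.84), a gain of 15 percentage points, m = 28, ICC 0.003 (maternal) or 0.013 (newborn), autocorrelation 0.8, loss 4%.

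**Reproducing the plan.** n = (2.24 + 0.84)² × [p1(1−p1) + p2(1−p2)] / 0.15², then × d_c × d_r, then / 0.96. The printed formula for r is a missing figure; r = mρπ/(1 + (m−1)ρ) returns the stated 0.062 for ANC.

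- ANC: 9.4864 × (0.2327×0.7673 + 0.3827×0.6173) / 0.0225 = 174.9. With d_c = 1.081 and d_r = 0.996, this gives 188.3. Then 188/0.96 = 195.8, so 196 per arm and 588 in total. Agrees.
- Exclusive breastfeeding: n = 118.1, d_c = 1.351, d_r = 0.9535, product 152.1. Then 3 × 152/0.96 = 475. Agrees. (The printed r of 0.251 does not match the stated d_r of 0.953; r = 0.216 does. N is unaffected.)

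The arithmetic is therefore sound, and it confirms that the 15% effect is absolute. It holds for these two indicators only.

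**Power for the composites.** At 188 analysed per arm, SE = √{[p1(1−p1) + p2(1−p2)] × d_c × d_r / 188} and power = Φ(difference/SE − 2.2414). The composite control proportions below are assumptions, because the article gives none.

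Newborn composite, +15 points, ICC 0.013. Worked case at 40%: variance sum 0.24 + 0.2475 = 0.4875; SE = √(0.4875 × 1.2882/188) = 0.0578; 0.15/0.0578 − 2.2414 = 0.354; power 64%. Women needed for 80%: 9.4864 × 0.4875/0.0225 = 205.5; × 1.2882 = 264.8; × 3/0.96 = 827.

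| Control proportion | Power | Women for 80% |
|---|---|---|
| 15% | 81% | 573 |
| 30% | 67% | 777 |
| 40% | 64% | 827 |
| 50% | 65% | 810 |
| 60% | 70% | 726 |
| 70% | 81% | 573 |
| 74.8% (breastfeeding alone) | 88% | 475 |

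The requirement peaks at about 830 women, near a control proportion of 42.5%.

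Maternal composite, ICC 0.003. The implied odds ratio is (0.3827/0.6173)/(0.2327/0.7673) = 2.04. The lowest control proportion shown, 3.9%, is 0.2327 × 0.48 × 0.35, using the facility-birth and early-PNC rates in the Background as if the components were independent. Worked case at 10%, +15 points: variance sum 0.09 + 0.1875 = 0.2775; SE = √(0.2775 × 1.0768/188) = 0.0399; power = Φ(3.762 − 2.2414) = 94%.

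| Control proportion | +15 points | +10 points | Odds ratio 2.04 |
|---|---|---|---|
| 3.9% | 99% | 86% | 23% |
| 5% | 98% | 82% | 29% |
| 10% | 94% | 66% | 52% |
| 15% | 88% | 55% | 67% |

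**Minimum detectable difference.** Solving difference/SE = 2.2414 + 0.8416 at 188 per arm gives about 16.5 to 17.8 points for the newborn composite at control proportions of 30-60%, and about 9.0 to 13.4 points for the maternal composite at 3.9-15%.

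**The case against.** The strongest reply is that the mismatch need not cost power. The planned effect is an absolute 15 points. On that effect, every maternal control proportion below 23.27% gives at least the planned power, because the binomial variance shrinks. Low maternal power appears only with a smaller gain or a constant odds ratio. The sizing does not assume a constant odds ratio, although the Data Analysis Plan does report effects as odds ratios. On the newborn side, 30-60% brackets the point of greatest variance; at 15% or 70% power is about 81%. All of this stands, so a reader who infers that the trial is underpowered for its primary outcomes goes further than the document allows.

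The 3.9% is also only a marker. It multiplies rates from different sources under independence, and positive correlation between using ANC, facility birth and PNC would raise it.

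A further reply is that the ANC section limits the 588 to ANC as the primary outcome, so no power is claimed for the composite. That is a fair reading of the section, but ANC visits alone are not a primary outcome in the Abstract, Outcomes or Operational Definitions. Reading the trial as testing components separately does not help either, since the Discussion's target is 8 visits, not more than 4.

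Finally, end-line data collection was complete, so N cannot change, and confidence intervals will show imprecision. This limits the remedy to restating the claim but does not remove the conflict.

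**Conclusion.** The concern holds as a mismatch between the outcomes sized and the outcomes defined. The article's own text is enough to establish it, and no other section reconciles it. The 80% power is a property of the two sized indicators and is not established for either composite.

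The direction of the error is not established. For the newborn composite the shortfall at a 15-point gain could be 10 to 16 percentage points of power if the control proportion lies in the middle range, or nil near 15% or 70%. For the maternal composite a full 15-point gain would be well powered, but from 3.9% it means a rise to 18.9%, nearly fivefold, and the article gives no ground for expecting that; smaller gains are often well below 80%. All these figures rest on assumed control proportions, on the protocol's ICCs carrying over to the composites, and on a normal approximation.

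**What to change.** 1. State in Sample Size Determination that the 80% power applies to more than 4 ANC visits and to exclusive breastfeeding, not to the composite primary outcomes.
2. For each composite as defined, report power or the minimum detectable difference at 196 per arm (188 analysed) over a stated range of control proportions and ICCs, using both design effects. The baseline survey can inform the range only through earlier births, because the women were 16-20 weeks pregnant at enrolment.
3. Report more than 4 ANC visits, exclusive breastfeeding and each other component as named secondary outcomes with their own estimates and confidence intervals.

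The cost is a recalculation and some wording, and possibly a less favourable stated power. No new participants or data are needed.

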#### Sample Size for Newborn Practice

For newborn care practice, the same procedure described earlier was used. First, the individual randomization sample size was calculated to be 118 based on the following assumptions: P1—the proportion of exclusive breast feeding among the control group of 74.8% [38], power=80%, 2-sided α of 0.025, effect size=15%, and *Z*α/2 adjusted for multiple comparisons using a Bonferroni correction=2.24. Then, the design effect (*d*_c_) due to cluster randomization was calculated as *d_c_* = 1 + (*m* – 1)*ρ* = 1.35 by considering the following parameters: within-period *p* of 0.013 [39] and cluster size assumed to be 28. The design effect due to repeated assessment was calculated as *d*_r_=(1–*r*^2^)=0.953, where the correlation between samples from the same cluster at different times *r*=0.251 by using assumptions: within-period ICC=0.013 [39], autocorrelation coefficient (π) of 0.8 (to allow for a 20% decay of the correlation from within to between different periods) [37], and *m*=28. By inflating the sample size under individual randomization with the 2 design effects as (n×*d*_c_×*d*_r_)=152. Considering a 4% loss to follow-up, the total sample size was 475.

Therefore, the sample calculated for ANC was larger (588) and was the final sample size of the trial to arrive at 21 clusters (7 per arm) and an average of 28 eligible pregnant mothers.

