### Data Analysis Plan

Double-data entry was accomplished using Epi-data (version 4.6, released in 2020; the EpiData Association) and exported to the SPSS (version 25; IBM Corp) for analysis. The report of this study will be made according to the CONSORT-EHEALTH (Consolidated Standards of Reporting Trials of Electronic and Mobile HEalth Applications and onLine TeleHealth) standards for reporting randomized controlled trials. Exploratory subgroup analysis was done to identify whether the effects of intervention vary with sociodemographic characteristics, socioeconomic characteristics, obstetric history, and psychological factors. To assess the characteristics of the study population through the lenses of different variables, selected data were tabulated by study arms; this helped us to identify variations and similarities among study arms. The summary statistics used for categorical variables were frequencies and percentages. For continuous variables, the mean and standard deviation will be presented.

To observe the effectiveness of mobile phone messaging-based message framing interventions for improving maternal and newborn health service usage, we will use an intention-to-treat approach where all randomized participants will be included in the statistical analysis, regardless of whether they received the intervention or not. A generalized linear mixed model will be used to adjust for both the clustering effect and the participant-level intracluster correction. The outcome variables are assumed to have a multivariable normal distribution. The odds ratio will be used to measure the effectiveness of the intervention on the outcome variable with a 95% CI.

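### The 80% power stated for antenatal care visits uses normal quantiles with 7 clusters per arm; on the protocol's own inputs it is about 69-73% with cluster-based degrees of freedom

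*Protocol article*

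**What the plan says.** The section on sample size for the ANC visit takes as its control value "the proportion of women attending ANC for more than 4 visits among the control group 23.27" per cent, with "power=80%, 2-sided α=0.025, effect size=15" per cent, and a critical value "adjusted for multiple comparisons using a Bonferroni correction of 2.24". The ICC "was assumed to be 0.003" and "the cluster size (m) was assumed to be 28". A second design effect, for repeated assessment, uses a cluster autocorrelation of 0.8 "to allow for a 20% decay of the correlation from within to between different periods". The product is 188 women per arm, raised to 196 for 4% loss, or 588 in all.

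The section on newborn practice repeats the method with its own inputs (control 74.8%, ICC 0.013), obtains a smaller total of 475, and concludes that the ANC figure "was the final sample size of the trial to arrive at 21 clusters (7 per arm) and an average of 28 eligible pregnant mothers".

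For the analysis, the Data Analysis Plan states: "A generalized linear mixed model will be used to adjust for both the clustering effect and the participant-level intracluster correction".

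**The concern.** Kebeles are the randomized units. A comparison of one message arm with control rests on 14 of them, and on 21 if the variance is pooled over the three arms. Multiplying by a design effect makes the variance larger, as it should, but treats that variance as known. Here it has to be estimated from few clusters, and a normal quantile ignores that uncertainty. The usual allowance is a t quantile on cluster-based degrees of freedom or an added cluster per arm. The article states neither, and its figures reproduce without either.

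The 80% will be relied on when results are read. If ANC shows no clear effect, readers will treat that as evidence from a trial with a one-in-five chance of missing a 15-point difference. With cluster-based degrees of freedom the chance is between about one in four and three in ten.

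**Working it through.** **Inputs** (from the two sample size sections): p1 = 0.2327; difference 15 percentage points, so p2 = 0.3827 (the absolute reading is the one that reproduces the stated n); two-sided alpha 0.025; power 80%; ICC 0.003; m = 28; autocorrelation 0.8; 7 clusters per arm; 188 evaluable per arm.

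**1. Reproduce the protocol's figure.**
- Variance sum: 0.2327 × 0.7673 + 0.3827 × 0.6173 = 0.4148.
- Individually randomized n = (2.24 + 0.84)² × 0.4148 / 0.15² = about 175.
- Clustering: 1 + 27 × 0.003 = 1.081.
- Repeated assessment: r = 28 × 0.003 × 0.8 / 1.081 = 0.062; 1 − r² = 0.996.
- Product: 175 × 1.08 × 0.996 = 188.2 (stated 188). With 4% loss: 188 / 0.96 = 195.8 (stated 196).

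The figures reproduce with the unpooled formula and normal quantiles. The pooled formula gives 192.8 after both design effects.

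**2. Power at 188 per arm.**
- Non-centrality = 0.15 / √(0.4148 × 1.081 × 0.9961 / 188) = 3.08.
- Degrees of freedom: 2 × (7 − 1) = 12 for a pairwise contrast; 3 × (7 − 1) = 18 if all arms contribute to the variance.
- t power is taken from the non-central t distribution.

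| Reference | Critical value | Power |
|---|---|---|
| Normal | 2.24 | 79.8% |
| t, 18 df | 2.45 | 73.2% |
| t, 12 df | 2.56 | 69.5% |

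If all 196 per arm were retained, these become 81.6%, 75.1% and 71.4%. For scale, at about 26.9 evaluable women per cluster, 8 clusters per arm give 77.4% (14 df) to 80.4% (21 df), and 9 give 83.5% (16 df) to 85.7% (24 df). The gap is thus one to two clusters per arm.

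**3. Newborn care at the enrolled number.** With 74.8% to 89.8%, ICC 0.013 and 188 evaluable per arm, the same method gives 79.3% (12 df) to 82.6% (18 df).

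**4. A mixed-model-type test.** Because the planned analysis is a mixed model, it was approximated by simulation: beta-binomial data, 7 clusters of 27 per arm, both message arms at 38.27% for power, a linear variance-component estimate that cannot go below zero, nominal level 2.5%. The simulation has no baseline period, so it omits the small repeated-assessment gain. At ICC 0.003:

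| Reference for the test | Type I error | Power |
|---|---|---|
| Normal | 2.3% | about 75% |
| Satterthwaite-type df | just under 2% | 71% |
| Fixed 18 df | 1.4% | 68% |

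The cluster variance was estimated as zero in about 45% of runs. With 28 per cluster, that is with no loss, the normal-referenced test has about 77% power. As the ICC rises, its type I error passes the nominal 2.5%: about 3.1% at ICC 0.013 and 3.6% at 0.05.

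**5. Sensitivity, not the protocol's ANC input.** If ANC had ICC 0.013, the design effects would be 1.351 and 0.9535. The non-centrality falls to 0.15 / √(0.4148 × 1.351 × 0.9535 / 188) = 2.81. Power is then about 72% (normal), 65% (18 df) and 61% (12 df).

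**The case against.** The strongest reply is that 69-73% belongs to a test on cluster-based degrees of freedom, whereas the protocol plans a mixed model. At ICC 0.003 almost all the variance is within clusters, and a mixed-model test referred to the normal distribution keeps its error rate. This stands. A reader might infer that 69-73% holds whatever the analysis; it does not, and about 75% is the figure for that test. It is still below 80%. The safe error rate also depends on the true ICC being as small as assumed, which the analyst will not know.

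It also stands that a fixed 18 df should not be imposed: at the protocol's own ICC it is conservative and costs power.

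Other stronger readings are not supported:
- **That the whole trial falls short.** The cluster count is stated in the newborn section, but newborn care keeps about 79-83% because the ANC calculation enlarged the trial.
- **That power is near 60% on the protocol's own inputs.** That needs ICC 0.013, which the protocol assumes for newborn care from a different source.
- **That there is an arithmetic slip.** The stated 188 and 196 follow from the stated method; the fault lies in the choice of quantile.
- **That the analysis section is deficient in not naming a reference distribution.** That detail commonly sits in an analysis plan, and the article does not say that a normal reference will be used.

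Finally, enrolment and end-line are complete, so the design cannot change. That limits the remedy to reporting and analysis, which the article describes as still pending.

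**Conclusion.** The point holds for ANC, the outcome that set the sample size. The stated 80% is about 7 to 10 points too high with cluster-based degrees of freedom (69-73%), and about 5 points too high for a large-sample mixed-model-type test (about 75%). No analysis examined reaches 80% at the 188 evaluable women for whom it is claimed.

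This takes the protocol's ICC, autocorrelation, 15-point difference and 4% loss as given, with equal cluster sizes. The t range reflects the choice between 12 and 18 df; the 75% rests on a linear approximation to the planned model. The matter is worth correcting because the figure is relied on and restating it is cheap. It does not invalidate the design.

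**What to change.** - Restate ANC power as about 70% at a 15-point difference: 69-73% with cluster-based degrees of freedom, at most about 75% with a large-sample mixed-model test at 188 evaluable per arm. Say that newborn care stays at about 79-83% at the enrolled number.
- Show ICC 0.013 for ANC only as a labelled sensitivity assumption: about 61-65% with cluster-based degrees of freedom, 72% with normal quantiles, repeated-assessment factor included.
- Analyse with a mixed model that has a small-sample correction, for example Satterthwaite degrees of freedom, because a normal reference exceeds its level as the ICC rises. Add a permutation test over the 21 kebeles as a check.

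The cost is a less favourable power statement, slightly wider intervals, a software option and one extra analysis. No new clusters or data are needed.
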